# Six weeks of home enteral nutrition versus standard care after esophagectomy or total gastrectomy for cancer: study protocol for a randomized controlled trial

**DOI:** 10.1186/1745-6215-15-187

**Published:** 2014-05-24

**Keywords:** Enteral nutrition, Feasibility, Gastrectomy, Gastric cancer, Jejunostomy, Qualitative, Esophageal cancer, Esophagectomy

## Abstract

**Background:**

Each year approximately 3000 patients in the United Kingdom undergo surgery for esophagogastric cancer. Jejunostomy feeding tubes, placed at the time of surgery for early postoperative nutrition, have been shown to have a positive impact on clinical outcomes in the short term. Whether feeding out of hospital is of benefit is unknown. Local experience has identified that between 15 and 20% of patients required ‘rescue’ jejunostomy feeding for nutritional problems and weight loss while at home. This weight loss and poor nutrition may contribute to the detrimental effect on the overall quality of life (QoL) reported in these patients.

**Methods/Design:**

This randomized pilot and feasibility study will provide preliminary information on the routine use of jejunostomy feeding after hospital discharge in terms of clinical benefits and QoL. Sixty participants undergoing esophagectomy or total gastrectomy will be randomized to receive either a planned program of six weeks of home jejunostomy feeding after discharge from hospital (intervention) or treatment-as-usual (control). The intention of this study is to inform a multi-centre randomized controlled trial. The primary outcome measures will be recruitment and retention rates at six weeks and six months. Secondary outcome measures will include disease specific and general QoL measures, nutritional parameters, total and oral nutritional intake, hospital readmission rates, and estimates of healthcare costs. Up to 20 participants will also be enrolled in a qualitative sub-study that will explore participants’ and carers’ experiences of home tube feeding.

The results will be disseminated by presentation at surgical, gastroenterological and dietetic meetings and publication in appropriate peer review journals. A patient-friendly lay summary will be made available on the University of Leicester and the University Hospitals of Leicester NHS Trust websites. The study has full ethical and institutional approval and started recruitment in July 2012.

**Trial registration:**

UKClinical Research Network ID #12447 (Main study); UKCRN ID#13361 (Qualitative sub study); ClinicalTrials.gov #NCT01870817 (First registered 28 May 2013)

## Background

Each year 13,500 patients in the United Kingdom are diagnosed with esophagogastric cancer [1]. Approximately a quarter of these patients will undergo surgery, with an ensuing median survival of around 2.5 years. Overall, after surgery 30% of patients will be cured of their cancer [2].

Nutritional support is considered important from diagnosis, through treatment, and in the palliative stages of the disease. Feeding tubes (jejunostomy (JEJ)) inserted into the small bowel during surgery allow early postoperative nutrition while patients are nil by mouth. JEJ are recommended by international groups [3] as they have been shown to have a positive impact on clinical outcomes in short-term studies [4-6]. Despite this, the proportion of patients having a feeding jejunostomy inserted varies greatly between NHS centers across the country [7] and the timing of discontinuing JEJ feeds is variable and not always related to the adequacy of oral nutritional intake [8]. The effect of supplementary JEJ feeds on oral intake has not been prospectively assessed but it is routine for tube feeds to be discontinued one to two weeks post-surgery in the belief that this will help promote a return to eating.

At University Hospitals of Leicester NHS Trust it is observed practice that 15 to 20% of patients require ‘rescue’ JEJ feeds to be re-instigated post-discharge due to failing nutrition. This can require readmission to hospital. The prevalence of home JEJ feeding after esophagogastric cancer surgery has been reported at between 15 and 48% in published studies that have employed home JEJ feeding [9-11]. It is unclear whether the practice of feeding all patients by JEJ at home would be beneficial. Studies that report medium-term endpoints are lacking and are required to provide evidence of the benefits of adjunctive nutrition support in this patient group

Few studies have assessed the potential benefits of continuing supplementary JEJ feeds after hospital discharge [12]. In an institutional review of practice [13] comparing the historical practice of not providing home enteral support with the recent practice of home jejunostomy feeding, home enteral support was associated with better weight maintenance. The effect of enteral nutrition on other outcome measures such as quality of life is not known.

Following esophagectomy or total gastrectomy patients often struggle to establish an adequate nutritional intake orally due to a combination of poor appetite, a fear of eating, early satiety, abnormal gut transit, gastrointestinal symptoms such as nausea, reflux, and altered bowel habits.

Studies have shown that over 60% of patients have an inadequate oral intake at time of hospital discharge, consuming 70 and 65% of their energy and protein requirements respectively [14]. An earlier study evaluating patients six months after esophagectomy demonstrated that 64% of patients reported a loss of greater than 10% of their baseline body mass index [15]. Estimates of the time taken to establish what would be considered a socially acceptable diet after surgery are around six months [16].

Weight loss and poor nutritional intake may contribute to the detrimental effect on overall quality of life (QoL) reported in these patients [17]. Although in general, tumor location and stage of disease are the major determinants of QoL, in esophageal cancer patient nutritional factors (dietary intake and weight loss) have been shown to be as important in determining functional QoL scores [18]. Global quality of life scores have been correlated with both postoperative BMI and weight loss [19].

Little is known about the patient experience of home tube feeding and studies often focus on heterogeneous populations of variable age and dependency [20]. In esophagogastric patients, the JEJ tube already remains in place but any additional effect of using it is not known. The effect on family and carers and their relationship to the patient must also be considered as home tube fed subjects are often reliant on support, and carers perceive QoL very differently to that of the patient [21,22]. This may increase the burden of treatment.

The aim of the current study is to pilot an investigation of the impact of six weeks of home JEJ feeding in patients undergoing esophagectomy or total gastrectomy for cancer and assess the feasibility of conducting an appropriately powered multi-centre trial to evaluate the effectiveness of six weeks of home JEJ feeding. Specifically this study will: (1) estimate participant recruitment and retention rates in order to inform a larger multi-centre trial, (2) estimate variability in disease-specific and general QoL measures, (3) explore the relationship between disease-specific and general QoL measures, (4) explore the effect of home feeding on nutritional parameters and total and/or oral intake, (5) estimate hospital readmission rates, (6) explore participants’ and their carers' experiences of living with a jejunostomy tube *in situ* and that of home tube feeding, (7) test the feasibility of estimating healthcare costs, (8) provide preliminary evaluation of the cost-effectiveness of postoperative home jejunostomy tube feeding compared with standard care from an NHS and personal social service.

## Methods/Design

### Study design and setting

This is a pilot prospective two-arm mixed-method randomized controlled trial (RCT), with treatment-as-usual as the control. Given the nature of the intervention and control it is not possible to blind participants or those responsible for patient care. To minimize bias the research dietitian who will collect study data will have no involvement in patient care. This study will be conducted at a single site, University Hospitals of Leicester NHS Trust, which draws patients from Leicester, Leicestershire and Northamptonshire.

### Trial management group

A trial management group has been setup including the investigators, representatives from the Leicester Clinical Trials Unit, and two former patients (one with their partner). This group will meet every six months for the duration of the study to review study progress.

### Participants

This study will recruit adult patients referred to the University Hospitals of Leicester NHS Trust Esophagogastric Cancer Service with a confirmed diagnosis of esophagogastric cancer, deemed suitable for an esophagectomy or total gastrectomy. The inclusion criteria are adults over 18 years of age with a confirmed diagnosis of esophagogastric cancer who are undergoing a planned curative surgical treatment esophagectomy (Ivor Lewis, three stage, or transhiatal resection) or total gastrectomy with placement of jejunostomy feeding tube. Patients will provide written informed consent for participation in the study.

The exclusion criteria include an inability to provide informed written consent, patients in whom artificial nutrition support at home is deemed inappropriate by either the patient or healthcare team (due to safety issues or home circumstances) and patients undergoing subtotal gastrectomy (would not usually have jejunostomy tube fitted).

Participation in this study does not exclude participation in national trials of perioperative chemotherapy. Due to the different scheduling arrangements the two treatment interventions (chemotherapy and jejunostomy feeding) would not be administered concurrently. The time frame for the administration of preoperative chemotherapy is prior to the planned six week jejunostomy feeding period, and the time frame for the administration of postoperative chemotherapy is after completion of the planned six week jejunostomy feeding. Some participants and their carer or partner will also participate in the qualitative study, for which the only additional criterion is a willingness to participate.

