### Recruitment

Potential participants will be identified at the weekly multidisciplinary, upper gastrointestinal cancer meetings by a team member involved in the patient’s care. At the surgical clinic potential participants will asked by a member of the healthcare team whether they are happy to receive information about the study. If they agree they will be provided with a participant information leaflet either by a member of the research team (if available) or the clinical team, and asked to give their consent for a member of the research team to contact them by telephone. A minimum of 24 hours later a member of the research team will contact the potential participant by telephone. If they agree to take part they will be visited in hospital at their pre-assessment clinic appointment. Those patients who do not wish to be contacted by telephone can inform their clinician that they wish to take part or telephone the research team.

Potential participants for the qualitative exploratory study will be those recruited into the RCT and their carers. At the initial recruitment stage participants will be asked to indicate on the consent form if they agree to be interviewed. Following the six-week intervention period, potential participants will be contacted and invited to be interviewed. Where a partner or main carer is identified, they too will be asked if they are interested in participating. On agreement, a volunteer information sheet will be posted out and consent will be taken prior to the interview taking place. It is envisaged that including the partner or carer will add to the depth of information, particularly regarding experiences of home tube feeding. The sample will also include male and female patients without family or support at home. Participants will be given the option to be visited at home or to attend the hospital for interview. Recruitment to the study will be conducted over a 20-month-period and individual participation in the study will last for 7 months.

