### Sample size

Home JEJ feeding is not routinely carried out at present and there is no published data on the variables of interest in this patient population. Consequently the sample size in this pilot study was chosen to enable a sensible estimation of the quantities of interest, in particular variability, whilst not exposing too large a number of participants to the full range of experimental procedures.

We therefore aim to recruit 60 subjects, 30 randomized to home JEJ and 30 to treatment-as-usual, which (allowing for up to 17% early withdrawal) would result in 50 participants completing the 6-week intervention period.

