## Outcome measures

### Quantitative data

The primary outcome measures in this pilot study have been chosen to determine whether or not an appropriately powered definitive trial will be possible. To this effect, the primary outcome measures are recruitment and retention rates at six weeks and six months post-baseline. Additional measures to be recorded at discharge, six weeks, three months and six months after baseline focus on the nutritional status and quality of life, specifically (1) nutritional parameters of weight, body mass index, upper arm anthropometry, and grip strength, (2) nutritional intake to include total energy (kcal/d) and protein intake (g/day), contribution of oral intake (food, fluids), oral nutritional supplements, and JEJ feed, (3) postoperative complications, (4) QoL using the European Organization for Research and Treatment of Cancer (EORTC) generic cancer questionnaire (QLQ-C30)[25] and the EORTC disease specific (esophagogastric) questionnaire (QLQ-OG25) [26].

To enable preliminary assessment of cost-effectiveness, QoL using the five domain EuroQol health outcome instrument (EQ-5D) [27] will be measured at three and six-months post-baseline and healthcare costs will be recorded for the duration of the study period. Survival data will also be collected at 12-months post-surgery.

Adverse events and serious adverse events will be defined in accordance with both the Medicines for Human Use (Clinical Trials) Regulations 2004 (SI2004/1031) and the subsequent amendment regulations (SI2006/1938) and ICH-GCP. Expected adverse events associated with the jejunostomy tube are blockage of the tube or inadvertent removal of the tube rendering feeding impossible and skin infection around the tube. Expected adverse events associated with the feed are bloating and diarrhoea.

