## Data analysis

### Quantitative data

As this is a pilot study and we aim to estimate a number of quantities necessary for the design and delivery of a definitive multi-centre trial, the estimates calculated will be presented along with 95% confidence intervals where appropriate. The proportion of eligible patients who consent to participate in the pilot will be calculated, along with the proportions in each intervention group completing six weeks and six months of assessments. Hospital readmission rates will be presented by intervention group. Variability of the QoL measures will be calculated, both by each group and pooled across both groups.

As it is anticipated that the likely outcome measure for the multi-centre trial will be QoL, a comparison of the QoL measure EORTC QLQ-C30 will be conducted using the Students t-test to compare the mean between the groups to provide a preliminary estimate of the treatment effect. Distribution of the data will be assessed graphically and if the normality assumption is considered to be unreasonable a non-parametric approach will be taken. A secondary analysis, using analysis of covariance (ANCOVA) and regression models will be conducted to adjust for type of surgery (used as a stratification factor in randomization) and baseline value of EORTC QLQ-C30.

The findings of the qualitative research may lead to a different outcome measure being proposed as the primary in the definitive trial and consequently the other QOL measures and other continuous outcomes at six weeks, three months, and six months will be analyzed similarly.

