## Discussion

Currently, there are no guidelines relating to the provision of home feeding after esophagogastric cancer surgery. Policy is determined at a local level with wide heterogeneity in UK practice. This pilot study is an essential precursor for the development of an appropriately powered multi-centre trial and will enable estimates of variability, recruitment and retention rates, and treatment costs, as well as inform choice of appropriate primary outcome for a multi-centre trial. Importantly it will also allow the acceptability of home JEJ to patients to be ascertained. By providing home feeding it is envisaged that more patient care would be delivered locally with a reduced need for hospital readmission for nutritional problems in the first months after surgery. This could represent a cost-effective use of NHS resources. If demonstrated to be beneficial, the findings of a trial assessing the effectiveness of home feeding would be applicable to the 1500 to 2000 patients undergoing esophagectomy or total gastrectomy annually in the UK, potentially saving costs to the NHS and improving the postoperative patient experience.

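### Patients who themselves judge home feeding inappropriate leave the denominator of the recruitment proportion, and nothing separates them from refusers

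*Protocol article*

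**What the plan says.** Four parts of the protocol article have to be read together.

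- **Eligibility (Participants).** The exclusions include "patients in whom artificial nutrition support at home is deemed inappropriate by either the patient or healthcare team (due to safety issues or home circumstances". Either party's judgement is enough, and the bracket names the grounds.
- **Primary outcome (Outcome measures, Quantitative data).** The article states that "the primary outcome measures are recruitment and retention rates at six weeks and six months post-baseline".
- **Definition (Data analysis, Quantitative data).** "The proportion of eligible patients who consent to participate in the pilot will be calculated". Consenters are the numerator and eligible patients the denominator.
- **Purpose (last paragraph of Background, and Discussion).** The study is to "estimate participant recruitment and retention rates in order to inform a larger multi-centre trial", and the Discussion adds: "Importantly it will also allow the acceptability of home JEJ to patients to be ascertained".

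The article does not say that patients excluded on their own judgement are counted as decliners, tabulated separately or added back in a second rate. The Recruitment section draws the interviewees only from people already in the trial and their carers, so the qualitative work does not reach this group either.

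**The concern.** A feasibility trial should show how many of the patients who could take part do take part, and why the others do not. Here one reason for not taking part, the patient's own view that home tube feeding would be unsafe or unworkable at home, is written as an eligibility criterion. Patients with that view drop out of both the numerator and the denominator.

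The Intervention section has the patient or a carer trained to run overnight pump feeds at home. Feeling unsafe with the pump, or having nobody to help, fits the bracketed grounds and is also an obvious reason to say no. The same person could be logged as ineligible or as a refuser, and the article gives no rule for deciding which.

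Two uses of the result are at stake. One is the conclusion about acceptability, because a high proportion among those who remain says little about those who ruled the intervention out. The other is a projection from the number of operations to the number of recruits, which needs the size of the self-excluding group.

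**Working it through.** **The plan's own figure.** The only sample-size figures are a target, "We therefore aim to recruit 60 subjects, 30 randomized to home JEJ and 30 to treatment-as-usual", and a withdrawal allowance of 17% that leaves 50 completers. 60 × (1 − 0.17) = 49.8, about 50. This reproduces and is not touched by the point. The article states no expected recruitment proportion, number eligible or number screened.

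**Notation.**

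- R = patients who consent. The target of 60 is used (Sample size).
- E = patients eligible as the article defines it. Not given; assumed to be 75, 100 or 120.
- X = patients who meet every other criterion but are excluded on their own judgement. Not given.
- f = X/(E + X), the share of otherwise eligible patients who self-exclude. Assumed to be 0 to 30%.

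**Formulas.**

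- Planned proportion = R/E.
- Proportion with self-excluders counted as decliners = R/(E + X).
- Ratio of the two = (E + X)/E = 1/(1 − f).

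The ratio does not depend on R or E. It exceeds 1 whenever X > 0 and equals 1 when X = 0.

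**Results with R = 60.**

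| f | Ratio 1/(1 − f) | E = 75 (planned 80%) | E = 100 (planned 60%) | E = 120 (planned 50%) |
|---|---|---|---|---|
| 0 | 1.00 | 80% | 60% | 50% |
| 5% | 1.05 | 76% | 57% | 47.5% |
| 10% | 1.11 | 72% | 54% | 45% |
| 20% | 1.25 | 64% | 48% | 40% |
| 30% | 1.43 | 56% | 42% | 35% |

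With E = 100 the gap runs from 3 percentage points (60 − 57) to 18 (60 − 42). For scale, the Wilson 95% interval for 60/100 is 50% to 69%. At f = 20%, X = 25 and the interval for 60/125 is 39% to 57%.

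**Effect on a caseload projection.** Take E = 100 and f = 20%. For every 100 patients who meet the other criteria, applying the planned proportion predicts 60 recruits, while counting self-excluders predicts 48. The difference can be removed only if X is known, and the outcome as defined does not supply it.

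**Effect on the accrual rate.** The Recruitment section states: "Recruitment to the study will be conducted over a 20-month-period". At one site, 60/20 = 3 recruits per month. Neither E nor X enters this figure.

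**The case against.** The strongest reply is that the bracket limits the exclusion to safety and home circumstances. On that reading a patient who simply dislikes tube feeding is still eligible and counts as a non-consenter, and an unsuitable home is an ordinary feasibility exclusion whoever reports it. This stands in part. A reader might infer that every reluctant patient is reclassified as ineligible, so that the rate is inflated by construction in proportion to how unacceptable the intervention is. The text does not support that. What remains is the patient who cites safety or home circumstances: that patient's own judgement suffices, and nothing separates it from a refusal.

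A second reply is that planning of the definitive trial is not harmed. Recruits per site per month already reflect every patient who was not recruited, and a later trial with the same criterion would see the same consent proportion among its eligible patients. Both statements are correct. A reader might infer that the definitive trial would be planned with too few sites or too short an accrual period; the documents do not support this, because the article nowhere proposes to apply the consent proportion to the whole caseload. The projection problem arises only if someone does so.

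A third reply is that a journal article commonly leaves the coding of a screening log to the full protocol. That is fair as to detail. But the criterion and the denominator are both stated here, and an analysis that follows them as written omits these patients.

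It might also be inferred that patients who decline the leaflet or the telephone call are dropped. Nothing in the Recruitment or Data analysis sections says so, and that is no part of this point.

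**Conclusion.** The point holds in a limited form. As written, patients excluded on their own judgement leave the denominator of a primary outcome, although their reluctance bears on the acceptability that the pilot claims to ascertain. The direction is certain if any such patients exist: the planned proportion is 1/(1 − f) times the one that counts them as decliners. The size is not known. The factors of 1.05 to 1.43 rest on an assumed f of 5% to 30%, for which the documents give no basis, and the effect is nil if nobody self-excludes. Neither proportion is the single true rate; they answer different questions, and a feasibility report needs both or needs to say which it gives. The harm is confined to judging acceptability and to projecting recruits from the surgical caseload. The accrual rate, the sample size and exclusions made by the healthcare team are not affected.

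**What to change.** 1. Keep exclusion by the healthcare team as ordinary ineligibility.
2. Record patient-judged exclusions as a separate category on the screening log, with the reason given.
3. Count these patients as eligible non-consenters in the recruitment proportion, or report the proportion both with and without them, each with a 95% confidence interval.

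No patient's care changes, and anyone may still decline. The cost is one screening-log category and one sentence in the outcome definition. The downside is that the reported recruitment rate may be lower. The reasons should be recorded at screening, because they may not be recoverable afterwards.
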